### Participant timeline

Enrollment was started January 10, 2022, and will be closed on December 31, 2023. Patients will be followed for at least three years after enrollment.

### Sample size

Given that the LORIS Study is a longitudinal observational study to describe the treatment patterns of LORA, the targeted sample size was not determined. A larger sample size increases the data confidence. According to the past record of each institution, it is expected that approximately 600–700 patients will be recruited.

### Recruitment

Patients who visit the study centers are requested to participate in the study by the attending rheumatologists if they are eligible based on the inclusion / exclusion criteria described above. Participants receive usual care according to site investigators’ discretion without any intervention from the study protocol.

### Data collection and management

After providing written informed consent, patients are enrolled in the registry. Clinical assessment data including physical examination, laboratory tests, and details of medication are recorded in the electronic data capture (EDC) system at each study center. The coordinating center will manage the EDC system.

Patients are asked to complete questionnaires to capture information regarding demographics and patient-reported outcomes. Present and past medical history are collected by nurses or trained clinical research coordinators and confirmed by site investigators. Clinical assessment data will be collected at baseline, Month 3, 6, 12, 18, 24, and 36. Questionnaires and interview surveys will be conducted at baseline, Month 12, 24, and 36. Detailed information of data collection is shown in Table 1.

**Table 1 Tab1:** Parameters captured by the registry database

Category	Items
Sociodemographic data	Age, sex, education, marital status
Medical history	Onset time Current symptoms of RA compared to those in the previous year Surgery for RA, site, type Total number of medications taken Vaccination history (*Streptococcus pneumoniae*, herpes zoster)
Medication	Use/non-use of MTX, start date, dose, reason for non-use (cognitive decline, interstitial pneumonia (IP), pulmonary diseases other than IP, renal dysfunction, hepatic dysfunction, history of infection, peripheral blood test results, complication/history of malignant tumor, and HBV carrier/infection, among others) Use/non-use of other csDMARDs Use/non-use of GCs, dose, administration period, and reason for administration Use/non-use of NSAIDs Use/non-use of opioids Use/non-use of molecular targeted drugs, start date, and dose Use/non-use of osteoporosis drugs (bisphosphonates, PTH preparations, denosumab, romosozumab, vitamin D preparations, and SERM)
Symptoms	Tender joint count (28・44) Swelling joint count (28・44) Physician global assessment (VAS) Patient global assessment (VAS) Physical function (HAQ-DI) Health-related QOL (EQ-5D-5L) Depression (PHQ-2) Pain and fatigue (VAS)
Laboratory data	Inflammation marker (CRP, MMP3, ESR) Blood cell count (White blood cell, neutrophil, total lymphocyte, red blood cell, hemoglobin, and platelet) Nutritional marker (Serum total protein, serum albumin, Hemoglobin A1c, serum total cholesterol, LDL, HDL cholesterol, TG) Infection tests (HBs antigen, HBs antibody, HBc antibody, HCV antibody, IGRA, and β-D-glucan) Autoimmune tests (rheumatoid factor, antinuclear antibody, anti-SS-A/Ro antibody, and anti-CCP antibody) Renal function (Serum creatinine, Serum cystatin C, eGFR-Cre) Liver function (AST or ALT) 25-hydroxy vitamin D (25OHD) Krebs von den Lungen-6 (KL-6)
Radiological examination	Plain X-ray (Xp) imaging (frontal and lateral chest, both upper and lower limbs, or all frontal images). The modified Sharp score will be calculated every year to assess the progression of joint destruction Bone density (DXA method, lumbar spine, or mean value for both sites)
Comorbidity	Malignant tumor (solid cancer, hematological cancer, among others, the presence or absence of metastasis) Lung disease (IP, COPD, pulmonary tuberculosis, atypical mycobacteriosis, bronchiectasis, or bronchiolitis, among others) Heart disease (myocardial infarction, other cardiovascular disease, chronic heart failure, or peripheral vascular disease, among others) Stroke Hemiplegia or paraplegia Hypertension Diabetes mellitus Hyperlipidemia (hypo-HDL-emia (< 40 mg/dl), hyper-LDL-emia (≥ 140 mg/dl), hypertriglyceridemia (≥ 150 mg/dl) Fracture (spine or femur, among others) Depression Gastrointestinal disease (peptic ulcer or colonic diverticulitis) Liver disease (hepatitis B, hepatitis C, or liver cirrhosis, among other liver dysfunctions) Renal disease (dialysis, decreased renal function [eGFR < 60]) Osteoarthritis (DIP, shoulder, elbow, knee, or hip joints) Herpes zoster Venous thromboembolism (pulmonary thromboembolism or deep vein thrombosis)
Lifestyle and health behavior	Smoking status Physical disability certification and the grade Certification of long-term care needs and the care level Social participation status Exercise habits
Physical examination	Height and body weight Grip strength Body composition (only at institutions where it is possible) Walk speed (only at institutions where it is possible, 10 m at comfortable walking speed) The five-times sit-to-stand test (only at institutions where it is possible)
Cognitive assessment	MMSE [17] will be performed for cognitive function assessment. It will be implemented on patients aged ≥ 75 years at enrollment, who are starting csDMARDs for the first time in this study, and when treatment contents are changed due to cognitive decline
Frailty assessment	Physical frailty based on J-CHS criteria [18] Kihon checklist [19–22] Questionnaire for medical checkup of old-old [23] Clinical frailty scale [24]

We will stop observation of the patient when he or she requests to withdraw from participation in the study, if there is no visit to the hospital for more than 6 months, or when the principal investigator determines that it is difficult to continue observation.

Enrollees are allowed to withdraw anytime. However, the data collected before consent withdrawal cannot be deleted and data of such enrollees will be analyzed or will be used secondarily.

Personal information enabling direct identification of any individual will only be handled by each research center. All data are sent to the study coordinator after anonymization.

The protocol of this study has been registered to the public clinical trial registration database UMIN-CTR (UMIN000046086) before the start of this study. Study results will also be updated and reported on the database as needed.

### Statistical methods

As registry implementation status, numbers of enrolled individuals, of patients whose data are obtained at each survey period, and of patients who have discontinued will be shown.

For variables related to patient background and treatment status, distribution will be shown by mean with standard deviation, median with IQR, or number and proportion in contingency tables.

The information of serious AEs and person-year will be obtained, and the survival rate with the 95% confidence intervals by treatment options will be estimated by person-year method. Serious AE requiring hospitalization, infectious AE, AE leading to death will be analyzed separately. Impact of baseline variables on each outcome will be investigated using multivariable analysis. A two-tailed *p* < 0.05 will be considered statistically significant. In addition, comparison between the age groups < 75 years old and ≥ 75 years old will be performed.

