### Patient and public involvement

Two patient representatives of the Japan Rheumatism Friendship Association [16] participated in the panel meeting to determine the study protocol on December 9, 2021. They are expected to join the second panel meeting which is planned in March 2024 to discuss the study results and build a consensus of treatment goals for LORA.

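### The by-treatment survival rate is to be estimated by the person-year method, which gives an incidence or mortality rate and equates to survival only if the hazard is constant

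*Protocol article*

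**What the plan says.** The Statistical methods section of the protocol article describes the data as follows: "The information of serious AEs and person-year will be obtained". It then states that "the survival rate with the 95% confidence intervals by treatment options will be estimated by person-year method" and that "Serious AE requiring hospitalization, infectious AE, AE leading to death will be analyzed separately". It gives no time point for survival and no assumption about the hazard. Baseline factors are to be examined by multivariable analysis with a two-sided 0.05 threshold.

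Safety of treatment is one of the two primary outcomes (Outcomes), and factors related to survival head the list beneath it.

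Three other statements govern how much follow-up each patient contributes:

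- Participant timeline: "Enrollment was started January 10, 2022, and will be closed on December 31, 2023", and "Patients will be followed for at least three years after enrollment".
- Data collection and management: observation stops on withdrawal, on the principal investigator's decision, or "if there is no visit to the hospital for more than 6 months".
- Patient and public involvement: patient representatives are expected at the "second panel meeting which is planned in March 2024 to discuss the study results".

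**The concern.** The sentence pairs a quantity with a method that does not estimate it. A person-year calculation returns events per unit of time at risk. To read survival at month t from a rate r one must write exp(−r·t), which is correct only when the hazard is the same throughout follow-up.

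If the hazard is higher soon after a drug is started than later, r is a weighted average, and the weights are set by how long patients happened to be observed. Two consequences follow. A survival figure derived from r can be wrong even within one treatment group. And two treatments with the same risk at every time since start can show different rates if their follow-up differs.

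These estimates bear on a primary outcome and are to be shown by treatment. The registry's findings are meant to feed a Delphi consensus and a guideline revision scheduled for 2024.

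**Working it through.** The article states no event rate, survival figure or target sample size, so there is no figure of the plan to reproduce. The check asks how far the person-year rate departs from survival, and under what conditions. All hazards, dropout rates and group sizes below are assumptions. Dates and planned follow-up are from the article.

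**1. Constant hazard.** At 6 per 100 person-years (PY), the expected rate is 6.00 whether follow-up is 0.5, 1, 2 or 3 years, and for dropout from 0 to 0.6 per year. exp(−3 × 0.06) = 0.835, which is the true three-year survival. There is no error.

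**2. Changing hazard, equal follow-up of T years.** Assume 0.20 per year for the first 0.5 year, then 0.08.

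- True survival: S(3) = exp(−(0.20 × 0.5 + 0.08 × 2.5)) = exp(−0.30) = 0.741.
- Expected events per patient by 3 years: 1 − 0.741 = 0.259.
- Expected person-years per patient: (1 − e^−0.10)/0.20 + e^−0.10 × (1 − e^−0.20)/0.08 = 0.476 + 2.050 = 2.526.
- Rate: 0.2592/2.526 = 10.26 per 100 PY.
- Implied survival: exp(−3 × 0.1026) = 0.735, an error of 0.6 points.

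The same formulae give 20.0, 14.2 and 11.3 per 100 PY for T = 0.5, 1 and 2 years. The rate falls with longer follow-up although the risk process is unchanged.

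**3. The March 2024 meeting.** Enrolment from 10 January 2022 to 31 December 2023 gives follow-up of 2.0 to 25.7 months at 1 March 2024 and 3.0 to 26.6 months at 31 March, so about 2 to 27 months. With uniform entry, no dropout and the hazards of step 2, the rate is 13.2 (1 March) or 13.0 (31 March) per 100 PY.

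| Month | Implied survival, exp(−r·t) | True survival | Difference |
|---|---|---|---|
| 12 | 87.6–87.8% | 86.9% | under 1 point too high |
| 24 | 76.8–77.1% | 80.3% | about 3 points too low |
| 36 (extrapolated) | 67.3–67.7% | 74.1% | 6 to 7 points too low |

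No patient could have 36 months of data at that cut.

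**4. Two treatments with identical risk.** Assume 325 patients each (half of 650, within the 600–700 expected), a hazard change at 6 months and a two-sided 0.05 Wald test on the log rate ratio.

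| Hazard, early then late (per 100 PY) | Rate ratio, 1 v 3 years of follow-up | Rejection | Rate ratio, 3 years planned, dropout 0.30 v 0.05 per year | Rejection |
|---|---|---|---|---|
| 6, 6 | 1.00 | 5.0% | 1.00 | 5.0% |
| 8, 5 | 1.18 | 9.6% | 1.03 | 5.2% |
| 10, 5 | 1.28 | 16.9% | 1.05 | 5.6% |
| 15, 5 | 1.49 | 43.1% | 1.09 | 6.9% |

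A spurious contrast therefore needs both a changing hazard and follow-up that differs by treatment. It is small when only dropout differs.

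**5. Death as a competing event.** Assume hospitalisation at 10 and death at 6 per 100 PY. Converting the hospitalisation rate with death censored gives 1 − exp(−0.30) = 25.9% at three years. The cumulative incidence is (0.10/0.16) × (1 − exp(−0.48)) = 23.8%. The 2-point gap arises only if rates are turned into probabilities.

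**The case against.** Person-year rates are a standard description of adverse events in registries, and a rate that stops counting time at death is a valid cause-specific rate. The article plans the same three-year minimum for every patient, and starting a first biologic or targeted synthetic drug is its own enrolment route, so planned follow-up is not shorter for those drugs. At full follow-up the survival error in step 2 is 0.6 points. The choice of model and the interval splits can be left to a full protocol or SAP. All of this stands, and it limits the consequence. It does not repair the sentence itself, which names an estimator for survival that estimates something else.

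A reader might infer three stronger claims that the documents do not support:

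- *That treatments with equal risk will appear different.* Both conditions in step 4 are needed, and the article states neither.
- *That rates could differ nearly twofold.* Comparing 6 with 36 months under the step 2 hazards gives 20.0/10.26 = 1.95. The enrolment window of about 24 months cannot by itself produce a 30-month gap in follow-up, and the article gives no figure for how often a biologic or targeted drug follows a conventional one.
- *That the plan mishandles death as a competing event.* It says only that the event types are analysed separately. It does not say that non-fatal rates will be converted to probabilities.

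**Conclusion.** The mismatch between the quantity named and the method named is certain from the text, and it concerns a primary outcome. Its numerical effect is conditional. There is none under a constant hazard. Under the assumed hazards of 20 then 8 per 100 PY, survival is about 0.6 points off at full three-year follow-up and about 3 points off at 24 months from a March 2024 cut.

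Comparisons between treatments can mislead where follow-up differs by treatment. Three routes are open: a March 2024 analysis, if treatments differ in when their patients entered; early stopping of observation that differs by treatment; and attribution of person-time to drugs started after enrolment, on which the article is silent. This should be corrected, but it does not invalidate person-year rates as a description of adverse events.

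**What to change.** Amend the Statistical methods section as follows:

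- Estimate all-cause survival by treatment with Kaplan-Meier and 95% confidence intervals at fixed months that the available follow-up supports: 12, 24 and, once reached, 36.
- If probabilities of hospitalisation or infectious events are reported, use cumulative incidence with death as a competing event.
- Keep the person-year results, label them incidence or mortality rates per person-year, and show them by time since treatment start, for example 0–6, 6–12, 12–24 and 24–36 months.

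The cost is a change of wording and a small amount of extra analysis in standard software. The event and censoring dates are already needed to compute person-years.

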### Consensus building

Based on the findings of the registry data analysis, consensus regarding treatment strategies of LORA will be built by using the modified Delphi process. Panel meetings consisting of the steering committee members, the representatives from each research centers, geriatricians, the experts of data management and RA patient representatives will be held to discuss about treatment strategies and goals. Eighty percent agreement within three rounds of discussion and voting is necessary to achieve consensus.

### Dissemination policy

The results of this study will be widely disseminated at domestic and overseas academic conferences, and in scientific papers. In addition, the results will be reflected in the JCR Clinical Practice Guidelines for the management of RA scheduled to be revised in 2024.

## Discussion

In LORA patients, both physicians and patient themselves tend to become overly cautious to AEs of DMARDs, which may lose opportunities to recover their ADL and QOL. It is well recognized that a considerable degree of caution is required when administering MTX to the elderly. Owing to the declining renal function with age, older patients may have a higher risk of complications due to MTX use [7]. Guidelines for MTX treatment have recommended starting at a low dose and setting a lower maximum dose for elderly patients but have not provided a clear criterion. Liver disorders, stomatitis, gastrointestinal disorders, cytopenia, and infections increase in a dose-dependent manner [25]. In the elderly patients with RA, the risk of developing lymphoproliferative disorders associated with MTX use is also known to increase [26]. In this study, we will monitor LORA patients who are starting MTX treatment carefully and determine the conditions in which treatment can be continued safely. We will also examine the factors that hamper continuing treatment and clarify the condition with which MTX are used appropriately.

As for b/tsDMARDs we have reported high patients’ satisfaction by conducting interview and questionnaire surveys [27, 28]. In these studies, some concerns regarding high medical costs as well as the increased risks of infection and malignancy have been disclosed. In the current study, we will compare the differences in patient characteristics AEs by treatment. It will clarify the appropriate conditions to use b/tsDMARDs.

Corticosteroids can be used even in patients who cannot tolerate DMARDs due to decreased renal function and other comorbidities, and it has been confirmed that the proportion of patients with prescription of corticosteroids tends to increase with age [29]. The minimum use of short-term corticosteroids in combination with csDMARDs in older patients with active early RA was weakly recommended by the guideline panels of the 2020 JCR guidelines [6]. Continuous use of corticosteroids causes osteoporosis, which directly lead to bone fractures, hospitalization, and the need for nursing care. Increased risk of severe infection due to corticosteroid use should also be warned. In this study, the use of corticosteroids and relevant patient background will be examined in detail to clarify acceptable dose and period of corticosteroids use in LORA.

### Limitations

Because of the observational study design, there are no comparator treatment group, which could make analyses of effectiveness and safety of treatments difficult. The evidence level obtained from this study will be evaluated low or very low by the Assessment, Development and Evaluation (GRADE) system. This study group is mainly comprised of the committee members of the 2020 JCR clinical practice guidelines for RA. The participants of this study will receive treatment from the expert rheumatologists so that treatment outcomes obtained in this study are expected to be superior to those at general medical facilities. In the absence of evidence regarding initial treatment for LORA, the elucidation of the level of prognosis that can be expected in the case of ideal treatment is essential to setting target values for RA treatment in Japan. To disseminate our findings to general outpatient clinics, we must need identifying the barriers for implementation (Additional file 1).

## Data Availability

The principal investigator of each research center keeps a record of data sharing with the joint research centers. When a third-party institution requests data sharing, the steering committee of this study shall review the study protocol and determine the permission and scope of data sharing.

## Abbreviations

ADL: Activities of daily living
AE: Adverse event
DMARD: Disease-modifying antirheumatic drugs
EDC: Electronic data capture
IP: Interstitial pneumonia
LORA: Late-onset rheumatoid arthritis
LORIS: Late-onset rheumatoid arthritis registry
QMCOO: Questionnaire for medical checkup of old-old
RA: Rheumatoid arthritis
RCT: Randomized controlled trials
